### Exercise test protocols

CPET and combined exercise echocardiography will be performed on a stationary cycle ergometer, since echocardiography should be performed at peak exercise [19]. Exercise echocardiography will be carried out after an overnight fast using a supine bicycle attached to a table tilted 30 to 45° to the left for best image acquisitions. Subjects will begin exercising at 25 W, and this will be increased by 25 W after 3 minutes. Workload in metabolic equivalent tasks will be calculated using a previously described standard equation for ergometer exercise [20]. Echocardiographic imaging will be performed continuously during each stage of the exercise protocol using a commercially available ultrasound system (GE vivid 7GE healthcare; Milwaukee WI, USA), and patients will be encouraged to exercise to maximum efforts. Breath-to-breath respiratory gas exchange will be continuously measured with a metabolic cart interfaced to the ergometer. Minute ventilation (V_E_, l/minute), carbon dioxide production (V_CO2_, ml/kg/minute), oxygen uptake (V_O2_, ml/kg/minute) and respiratory exchange ratio will be calculated. Peak V_O2_ is usually defined as the highest V_O2_ measured during the last minute of symptom-limiting exercise. The ventilatory anaerobic threshold will be determined using the V-slope method [21], and ventilatory efficiency will be determined by calculating the slope of the increase in ventilation with respect to carbon dioxide output (V_E_/V_CO2_), with values measured between at rest and the level of anaerobic threshold. To assess hemodynamic changes, echocardiography will be performed at rest and every 3 minutes during exercise by an expert echocardiographer with extensive experience of exercise echocardiography. LV dimensions, LV volumes, LV ejection fractions, mitral E and A velocities and corresponding E/A ratios, mitral annular E′, A′, and S′ velocities, E/E′ ratio, and pulmonary artery systolic pressure (obtained from maximal tricuspid regurgitation velocity determined using continuous wave Doppler) will be carefully obtained.

### Safety

Any participants with a hypersensitivity reaction to the study drug or an adverse event after study medication, those that do not want to remain in the trial, or those that comply with medication <80% will be dropped from the trial, as will those judged to be at risk due to participation in the trial by an attending physician.

Udenafil has been reported to be safe and well tolerated by healthy volunteers [17], and by patients with erectile dysfunction [14]. No serious adverse events occurred in either study. Common adverse events included nausea, headache, facial flushing, febrile sensation, penile erection, and eyeball pain, all of which have been reported to adverse events of other PDE5 inhibitors. Adverse events will be immediately reported directly to the study investigators, and study staffs will be obligated to manage these events. Patients will be interviewed at each visit about the occurrence of any adverse events, and onset time, duration, and severity will be recorded on case report forms. The possibility of causal relationships between the study drug and the intensities of adverse events will be evaluated by the investigators. The investigators are mandated to report serious adverse events to the institutional review board within 24 hours of recognition. A data and safety monitoring committee will monitor the safety of patients participating in the trial and all ongoing serious adverse events will be closely followed until these conditions have stabilized.

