### Study design and medications

Patient screening for trial eligibility will be based on reviews of medical records and echocardiographic results before baseline visits. After confirming study eligibility, baseline examinations (see the next section) will be conducted. Subsequently, patients will be randomized in a double-blind fashion to receive either udenafil or placebo (1:1) on top of any background therapeutic regimen in compliance with current recommendations [16], utilizing the randomization scheme depicted in Figure 2. An independent computer-generated list of random number will be used for participant allocations. Patients will receive either 50 mg udenafil or placebo twice daily for the first 4 weeks, and then if tolerated the dosage will be doubled to 100 mg twice daily for the next 8 weeks. Placebo and active study drugs (that is, udenafil) will appear to be identical and will be provided in blinded kits.

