**Figure 2 F2:**
[figure not shown]
**Study visit schedule of the ULTIMATE-SHF trial.** bid, twice daily; CPET, cardiopulmonary exercise test; Echo, echocardiography; Exercise Echo, exercise echocardiography; NYHA, New York Heart Association.

In the phase I trial, 42 healthy male volunteers received 25 to 300 mg of udenafil per day and experienced only minor adverse events [17]. Furthermore, a clinical trial on erectile dysfunction showed that 100 to 200 mg udenafil was well tolerated [18]. Because the half-life of udenafil is 7 to 9 hours, which is longer than that of sildenafil (4 hours), the study drug will be provided twice daily. Throughout the trial, medications prescribed by referring physicians will not be changed.

The ULTIMATE-SHF trial has been approved by the Clinical Research Institute at our hospital (H-1102-063-352), and the study drug, udenafil, has been approved as Investigational New Drug for therapeutic use in patients with chronic SHF, by the Korean Food and Drug Association.

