### Follow-up protocol

The trial duration is expected to be 3 months. Participants will attend study visits at screening, baseline, and weeks 4 and 12. At each visit, patients will undergo a complete physical examination, medical history-taking, and an assessment of drug compliance. Investigators will evaluate all clinical and laboratory adverse events at each visit. New York Heart Association functional class and predefined clinical events as described below will be recorded at each clinical visit. Venous blood will be drawn after a 15-minute rest period at screening, and at 4-week and 12-week visits, and will be subjected to the following test battery: B-type natriuretic peptide, complete blood count, electrolyte panel, serum creatinine, and liver function test. At screening visits, echocardiography will be performed at rest, and based on the results obtained study investigators will decide on patient eligibility. At baseline and at 12 weeks, participants will undergo CPET (V_Max_ 229 Respiratory Analyzer; SensorMedics, Homestead, FL, USA) and exercise echocardiography to evaluate exercise capacity in a quantitative manner. At all study visits, researchers will collect health-related information, such as adverse events, admission for acute decompensated HF, and change in medication. In addition, medication compliance of all participants will be carefully assessed by the pill-count method at every visit.

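### The Safety section removes participants from the trial for any adverse event, with no condition on severity, cause or tolerability

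*Protocol article*

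**What the plan says.** The opening sentence of the Safety section lists who leaves the study. One ground reads "Any participants with a hypersensitivity reaction to the study drug or an adverse event after study medication". Unwillingness to continue and medication compliance below 80% are two more. All of these "will be dropped from the trial". A further ground is added at the end: "as will those judged to be at risk due to participation in the trial by an attending physician".

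Other statements bear on how this works in practice:

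- **Safety**, on earlier udenafil studies: "Common adverse events included nausea, headache, facial flushing, febrile sensation, penile erection, and eyeball pain". The section describes these as known effects of other PDE5 inhibitors. Severity is recorded and causality evaluated, but neither is linked to the removal rule.
- **Study design and medications**: after 4 weeks at 50 mg twice daily, "then if tolerated the dosage will be doubled to 100 mg twice daily for the next 8 weeks". The phase I volunteers "experienced only minor adverse events".
- **Follow-up protocol**: "Investigators will evaluate all clinical and laboratory adverse events at each visit". Also, "At baseline and at 12 weeks, participants will undergo CPET".
- **Study withdrawals**: the investigator and the attending physician may, at their discretion, take a patient off trial treatment if continuing would harm the patient.
- **Table 2, item 11**: flushing, headache, febrile sensation, eyeball pain and similar reactions are secondary outcomes.
- **Sample size calculation**: 10% loss is allowed, assumed missing completely at random and so unrelated to the study variables.
- **Statistical considerations**: intention to treat, with all patients analysed according to randomization.

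**The concern.** A site that follows the sentence literally would remove a patient with a mild headache or flush, or with an incidental laboratory abnormality. These are the events the trial expects and plans to count.

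Maximal oxygen uptake is measured only at baseline and week 12, so a patient removed in between would probably have no primary outcome. Removal prompted by a drug effect could also be more common on udenafil. Loss of that kind depends on treatment, so it does not match the missingness assumed in the sample size. It also works against an analysis of everyone randomized, because the rule itself ends participation.

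**Working it through.** **Is the rule narrowed anywhere?**

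1. Physician judgement of risk, in the same sentence, is an additional ground. It does not qualify the adverse-event ground.
2. Study withdrawals gives discretion over trial treatment. The Safety rule is mandatory and concerns the trial. Neither refers to the other.
3. Dose doubling depends on tolerability. The two rules can be applied in sequence (first remove anyone with an event, then double the dose in those left), so they do not strictly contradict each other. Read that way, however, the tolerability condition has little left to do.
4. No section describes a week-12 test, or any other assessment, after a participant is dropped.

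The literal reading therefore stands. Loss of the week-12 test is an inference from being dropped and from point 4.

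**Reproducing the sample size.** Inputs from Sample size calculation: difference 16.1 − 14.0 = 2.1 ml/kg/minute, SD 2.5, two-sided 5% level, 80% power.

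- n per arm = 2 × (1.960 + 0.842)² × 2.5² / 2.1² = 22.25, rounded up to 23.
- With 10% loss: 23 / 0.9 = 25.6, rounded up to 26.
- Allowance for loss from all causes: 26 − 23 = 3 per arm.

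The stated 23 and 26 per group reproduce.

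**Power if more are lost.** Power = Φ( 2.1 / (2.5 × √(1/n₁ + 1/n₂)) − 1.96 ). The document gives no adverse-event rate, so the numbers remaining are assumed.

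| Placebo / udenafil with outcome | Power |
|---|---|
| 26 / 26 | 85.7% |
| 23 / 23 | 81.3% |
| 23 / 22 | 80.4% |
| 23 / 20 | 78.4% |
| 23 / 18 | 76.1% |
| 20 / 20 | 75.7% |
| 18 / 18 | 71.2% |

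For 23 / 18: √(1/23 + 1/18) = 0.3147; 2.1 / (2.5 × 0.3147) = 2.669; 2.669 − 1.96 = 0.709; Φ = 0.761. The formula takes no credit for the planned baseline adjustment (ANCOVA), which would raise these figures.

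**Bias.** A figure would need the number removed in each arm and how far those patients' outcomes, after baseline adjustment, would have differed from the outcomes of those kept. The document gives neither, so none is calculated.

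**The case against.** The strongest reply is that the sentence is loose English in a condensed article. Staff must manage adverse events and record their duration and severity, dose doubling presupposes patients who tolerate the drug, and withdrawal for harm is discretionary. All of this suggests that patients with events were expected to stay, and that the authors had serious or intolerable events in mind. Literally applied, the rule would also remove placebo patients for unrelated laboratory findings, which is unlikely to be the intention. This reply has weight and limits confidence. It does not remove the point: condensation excuses omissions, whereas here a rule is stated, and stated too broadly.

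A reader might infer more than the documents support:

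- *That every removed patient loses the primary outcome.* The article does not say so, and an event first reported at the week-12 visit need not cost the test.
- *That the clause targets mild events, because physician-judged risk is listed separately.* Withdrawal grounds often overlap, as hypersensitivity and risk do here, so overlap proves nothing about intent.
- *That removals will be more frequent on udenafil and bias the result in a known direction.* Class effects make an imbalance plausible, but no rate is given, and an all-cause rule would also remove placebo patients.
- *That the analysis would omit these patients.* Statistical considerations speaks only of omitting data missing completely at random. It does not say how these removals would be classified.

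**Conclusion.** The point holds as a badly drawn rule. As written, any adverse event after study medication leads to removal from the trial, and no other section limits this. The result is a poor fit with tolerability-based dosing, with discretionary withdrawal from treatment, and with the as-randomized analysis. If removals were related to study drug, the completely-at-random allowance of 3 per arm would not describe them.

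The effect on power is modest: about 5 percentage points between 23 / 23 and 23 / 18 (81.3% − 76.1% = 5.2), before any gain from ANCOVA. The possible selection effect matters more in principle, but its size and direction cannot be derived from the document. The conclusion rests on the literal reading and on the inference that dropped participants are not tested at week 12. Severity is minor and confidence moderate.

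**What to change.** Replace the whole first sentence of the Safety section with:

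*Study drug will be stopped for a hypersensitivity reaction, a serious or intolerable adverse event, or if the attending physician judges continued treatment to be a risk. Mild or tolerated adverse events are recorded and do not by themselves stop study drug. Patients who stop study drug or take <80% of it remain in follow-up unless they withdraw consent, have the week-12 CPET where safe, and are analysed as randomized.*

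The compliance ground has to change too. A patient who stops early for an adverse event would generally fall below 80% and be dropped under that ground instead. Study withdrawals should be aligned with this wording.

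No visit or test is added, because the week-12 test is already scheduled. The cost is that some tests are done off drug. If k of 26 udenafil patients stop and keep no benefit (worst case), the expected difference is 2.1 × (26 − k)/26, that is 2.02, 1.94 or 1.86 for k = 1, 2 or 3. Power at 26 per arm is then 83.0%, 79.8% or 76.4%, instead of 85.7%. The change is therefore not a way to gain power. It keeps randomized patients measurable, as the intention-to-treat analysis requires.

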### Study withdrawals

Patients will be permitted to request withdrawal from treatment at any time without providing reasons. The primary investigator and the attending physician will also have authority to drop patients from the trial treatment if it is considered that further participation in the trial would be detrimental to the patient's well-being. Such treatment withdrawals will be documented using a case report form and in patient's medical records. In addition, we have a plan to evaluate the results of this trial in the middle of this study, and based on these interim results the trial can be prematurely terminated if the drug effect would be highly suggested to be beneficial or harmful.

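### The Safety section removes patients from the trial, not only from study drug, after any adverse event or compliance below 80%, which conflicts with analysing everyone as randomised

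*Protocol article*

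**What the plan says.** The Safety section gives one mandatory rule with several triggers. The first is "Any participants with a hypersensitivity reaction to the study drug or an adverse event after study medication". Another is unwillingness to continue: "those that do not want to remain in the trial". The compliance trigger carries the consequence: "those that comply with medication <80% will be dropped from the trial". A physician's judgement that the patient is at risk has the same result. The only continued follow-up this section mentions concerns safety: "all ongoing serious adverse events will be closely followed until these conditions have stabilized".

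Study withdrawals uses narrower language. Patients may ask to stop treatment, and the investigator and attending physician have "authority to drop patients from the trial treatment" when continuing would harm the patient. It adds: "Such treatment withdrawals will be documented using a case report form". Study design and medications has a tolerability step: "if tolerated the dosage will be doubled to 100 mg twice daily".

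On the outcome, Follow-up protocol states: "At baseline and at 12 weeks, participants will undergo CPET". No other exercise test is scheduled after baseline. Study endpoints defines the primary outcome as the change in maximal VO2 between those two tests. Statistical considerations commits to intention-to-treat, with all patients analysed as randomised by a baseline-adjusted comparison (ANCOVA). Sample size calculation allows 10% loss and describes it as missing completely at random.

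**The concern.** A patient dropped before week 12 under the Safety rule has no primary outcome and cannot be analysed as randomised in any useful sense. Such losses also do not fit the Sample size section's description, because the rule selects patients on tolerability and adherence. Both arise after randomisation and udenafil can affect both. Headache, facial flushing and eyeball pain are listed in Safety as common effects of the drug, and Table 2 item 11 makes them secondary outcomes. Taken literally, recording such an outcome ends the patient's participation.

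If removal differs between arms and is related to exercise capacity, the comparison of remaining patients is biased. The direction cannot be known in advance: those removed might be sicker, or might be strong vasodilator responders. The rule may also make censoring informative for the clinical events in Table 2 item 10. A week-12 test that was never done cannot be recovered at analysis.

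**Working it through.** **1. The texts side by side**

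| Ground | Safety | Study withdrawals |
|---|---|---|
| Patient's wish | removed from trial | treatment withdrawal |
| Risk to the patient | removed from trial | treatment withdrawal |
| Any adverse event | removed from trial | not named |
| Compliance below 80% | removed from trial | not named |

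For the last two rows nothing softens the Safety wording, and neither section keeps these patients in follow-up to the week-12 test.

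**2. The plan's own sample size**

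Inputs (Sample size calculation): difference 16.1 − 14.0 = 2.1 ml/kg/min, SD 2.5, two-sided 5%, power 80%.

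n = 2 × (1.960 + 0.842)² × 2.5² / 2.1² = 22.25, rounded up to 23 per arm. Then 23 / 0.90 = 25.6, rounded up to 26. The stated figures reproduce.

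**3. Bias if removal is informative**

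From the protocol: 26 per arm, SD 2.5, ANCOVA of the week-12 value on arm and baseline among retained patients. Assumed, because the protocol gives no figures:

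- loss rates by arm (written udenafil/placebo, in %);
- baseline to week-12 correlation r of 0.5 or 0.7;
- correlation d between an underlying tendency to drop out and the outcome, 0.3 to 0.7. A patient drops out when that normally distributed tendency crosses a threshold set by the loss rate.

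In this model dropped and retained patients differ by d × SD × φ(z_p) / [p(1 − p)], where p is the loss rate and φ(z_p) the normal density at its quantile. For udenafil the extremes are:

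- d = 0.3, p = 0.40: 0.3 × 2.5 × 0.386 / 0.24 = 1.2 ml/kg/min
- d = 0.7, p = 0.20: 0.7 × 2.5 × 0.280 / 0.16 = 3.1 ml/kg/min

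The upper end is a strong assumption.

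Simulated results with no true effect, when dropped patients do worse (60,000 trials per cell; ranges over r and d):

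| Loss | False benefit, ml/kg/min | Type I error |
|---|---|---|
| 12/8 | 0.02–0.09 | 5.0–5.2% |
| 15/5 | 0.06–0.22 | 5.1–6.3% |
| 20/10 | 0.06–0.21 | 5.2–6.2% |
| 30/15 | 0.09–0.31 | 5.2–7.7% |
| 40/20 | 0.12–0.41 | 5.4–9.1% |
| equal, 20, 30 or 40% | within 0.006 of 0 | 4.9–5.1% |

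Hand check of one cell (20/10, r = 0.5, d = 0.3). Bias is approximately d × SD × (1 − r²) × [m(0.20) − m(0.10)], with m(p) = φ(z_p)/(1 − p). Here m(0.20) = 0.280/0.80 = 0.350 and m(0.10) = 0.1755/0.90 = 0.195. So 0.3 × 2.5 × 0.75 × 0.155 = 0.087, against 0.09 simulated.

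**4. The opposite direction**

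If dropped patients do better, a true effect of 2.1 is estimated as 2.01 (r = 0.5) or 2.04 (r = 0.7) at 20/10 with d = 0.3. At 40/20 with d = 0.7 it is 1.69 or 1.80, with power 69% or 87%.

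**5. Lost numbers alone**

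With uninformative loss (d = 0) and a true effect of 2.1, ANCOVA power at r = 0.5 and 0.7 is 89% and 97% at 10/10, 87% and 96% at 20/10, and 78% and 91% at 40/20. Smaller numbers are therefore not the problem.

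**The case against.** The best defence is that the protocol uses the two phrases loosely. Patient request and risk to the patient appear in both Safety and Study withdrawals, and the latter calls them withdrawal from treatment. Automatic removal at the first headache also fits poorly with a dose step that depends on tolerability, with recording the severity and duration of events, and with intolerance being an outcome. This stands as evidence of intent: literal removal for any adverse event is probably not what was meant. It does not cure the text. The Safety sentence applies one consequence to unwillingness to remain in the trial and to the other triggers alike, so a site can fairly take it at its word.

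The compliance trigger also has limited reach. Pills are counted only at visits. A count at week 12 falls at the visit where the exercise test is due, so among the scheduled post-baseline counts only week 4 can remove someone beforehand. That is correct and makes heavy loss from compliance alone less likely. Adverse events reported between visits can still cause early removal.

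The bias is small near the planned 10% loss: under 0.1 ml/kg/min at 12/8 and none at 10/10, against a design effect of 2.1. That stands too.

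Finally, follow-up after stopping drug is detail an article may leave to the full protocol. Silence alone would be no finding. The finding rests on what the Safety section states, which a fuller document would have to contradict rather than complete.

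**Conclusion.** The concern holds and should be fixed; confidence is medium. As written, a mandatory rule lets events that udenafil can cause decide who has a primary outcome, against the protocol's own commitment to analyse everyone as randomised and its assumption about losses. If only stopping drug was intended, the sentence is misworded. If removal was intended, it contradicts the analysis section. Either way it needs the same correction.

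The size depends on assumed drop rates and correlations. It is negligible with mild or balanced loss, and reaches 0.41 ml/kg/min of false benefit and 9.1% type I error only with heavy unequal loss strongly tied to outcome. The direction is unknown. No loss of planned power from reduced numbers is claimed. Nor is any conflict claimed with the sentence in Statistical considerations on omitting missing data, since it covers only data missing completely at random.

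**What to change.** Reword the Safety section so that a hypersensitivity reaction, an adverse event the investigator judges to require it, or compliance below 80% stops study drug only, in line with the treatment wording in Study withdrawals. State that every randomised patient who has not withdrawn consent attends the week-12 visit, with the exercise test if able and ascertainment of clinical events, and is analysed as randomised. Use the 80% limit only to define a per-protocol sensitivity set.

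In Sample size calculation, keep the 10% allowance, but do not describe outcomes still missing after an adverse event or non-compliance as missing completely at random. A sensitivity analysis for those outcomes is optional and can sit in the analysis plan.

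The cost is a wording amendment. It uses visits and tests already scheduled and adds no patients. Including patients who are off drug dilutes the effect somewhat, which intention-to-treat already implies. Trial status shows recruitment under way, so the sooner this is clarified, the fewer week-12 tests are at risk.
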